#### Sample size

2.5.1.

The CARRDIP randomized trial was designed to detect a clinically relevant difference in maternal cholesterol levels at week 36 in pregnancy and in neonatal cholesterol levels (26). In the CARRDIP20 study, we examined differences in CVD risk factors, which are typically in the range of 0.5–0.7 standard deviations (SDs) in intervention trials with groups randomized to different diets (45), requiring a sample size of approximately 64–100 per group with 80% power at a 5% significance level. Thus, despite the expected loss to follow-up, we most likely have statistical power to detect clinically relevant differences between the groups (46). If we assume an average difference in the systolic blood pressure of 5 mmHg, with SD = 10 mmHg, we will need 128 participants (64 in each group; power 80%, significance level 5%). This corresponds to 47% of the mothers that participated in the CARRDIP trial.

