### Participants

2.3.

The CARRDIP study included healthy, low-risk pregnancies to minimize possible confounding factors related to later CVD risk in the offspring. Eligible participants were included after an ultrasound showing a single healthy fetus in gestational weeks 17–20. The inclusion criteria were non-smoking pregnant women aged 21–38 years with a body mass index (BMI) of 19–32 kg/m^2^. The exclusion criteria were high-risk pregnancy due to diabetes mellitus, endocrine disease, chronic hypertension, drug abuse, history of thromboembolic disease, or significant gastrointestinal, cardiac, pulmonary, or hematologic disease. Of the 290 women included in the CARRDIP study, 21 women withdrew their consent before or during the intervention, leaving a final number of 269 mother–offspring pairs. All mothers and their offspring from the CARRDIP cohort will be invited to participate in the follow-up.

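### The sample-size paragraph pairs effects of 0.5–0.7 SD with 64–100 per group, but those effects need about 64 down to 34; one of the two ranges must be corrected

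*Protocol article*

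**What the plan says.** All the relevant statements but one stand in section 2.5.1 (Sample size) of the protocol article.

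- Differences in cardiovascular risk factors are given as a standardised range, "which are typically in the range of 0.5–0.7 standard deviations (SDs) in intervention trials with groups randomized to different diets".
- The requirement attached to that range is "requiring a sample size of approximately 64–100 per group with 80% power at a 5% significance level".
- The next sentence draws its conclusion from this: "despite the expected loss to follow-up, we most likely have statistical power to detect clinically relevant differences between the groups".
- A worked example follows: "If we assume an average difference in the systolic blood pressure of 5 mmHg, with SD = 10 mmHg". It arrives at 64 per group and 128 in total, at the same power and significance level.
- The example is then compared with the cohort: "This corresponds to 47% of the mothers that participated in the CARRDIP trial". The size of the cohort comes from section 2.3 (Participants), "leaving a final number of 269 mother–offspring pairs".

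**The concern.** Larger effects need fewer participants. By the section's own example, 64 per group is the requirement for 0.5 SD, which is the smallest effect in the quoted range. So 64 should be the upper end of the sample-size range, yet it is printed as the lower end, and the other end rises to 100.

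The sentence about adequate power is presented as a consequence of this line. The two ways of repairing the line put different demands on a fixed cohort of 269 pairs. A reader who wants to know what size of effect the follow-up can detect is therefore given two incompatible answers within one sentence.

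**Working it through.** **Inputs.** Effect 0.5–0.7 SD; power 80%; significance level 5%; worked example 5 mmHg with SD 10 mmHg and 64 per group (all section 2.5.1); 269 pairs (section 2.3). The section does not say whether the test is one- or two-sided. Two-sided is assumed, and step 1 supports this.

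**Formula.** For two equal groups, the normal approximation per group is n = 2(z₀.₉₇₅ + z₀.₈₀)²/d² = 2(1.960 + 0.842)²/d² ≈ 15.70/d². The exact two-sample t-test gives slightly more and is used below.

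**Step 1: reproduce the worked example.** d = 5/10 = 0.5. The approximation gives 15.70/0.25 = 62.8, so 63. The t-test gives 63.8, so 64 per group and 128 in total. This matches the protocol. A one-sided test would give about 50 per group, so the section is working two-sided. As a share of the cohort, 128/269 = 47.6%, in line with the quoted 47%.

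**Step 2: recompute the range.**

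| Effect (SD) | t-test n per group | Rounded up | Total |
|---|---|---|---|
| 0.4 | 99.1 | 100 | 200 |
| 0.5 | 63.8 | 64 | 128 |
| 0.6 | 44.6 | 45 | 90 |
| 0.7 | 33.02 | 34 | 68 |

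The stated effects need 64 down to 34 per group. The printed 64–100 matches 0.5 down to 0.4 SD.

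**Step 3: look for a reading that rescues the line.** Each row is for 0.5–0.7 SD.

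| Reading | Result |
|---|---|
| Totals instead of per group | 68–128 |
| One-sided 5% (normal approximation) | 26–50 per group |
| 90% power (t-test) | 44–86 per group |
| 95% power (normal approximation) | 54–104 per group |
| 1% significance level (normal approximation) | 48–94 per group |
| Inflated for 36% loss, n/(1 − 0.36) | 34 becomes 54, 64 becomes 100 |
| Inflated for 47% loss, n/(1 − 0.47) | 34 becomes 65, 64 becomes 121 |

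None gives 64–100. The section states no inflation rate, and no single rate fits both ends.

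**Step 4: power of the printed group sizes under the stated effects.**

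| Effect (SD) | 64 per group | 100 per group |
|---|---|---|
| 0.5 | 80.1% | 94.0% |
| 0.7 | 97.6% | 99.8% |

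**Step 5: what each repair asks of the cohort.** Keeping 0.5–0.7 SD means 68–128 attendees: 68/269 = 25% and 128/269 = 48%. Keeping 64–100 per group means 128–200 attendees: 48% and 200/269 = 74%.

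**The case against.** Four points can be made for the protocol.

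1. **The figure governs nothing.** All pairs from the original trial are to be invited, so neither recruitment nor analysis depends on whether the range reads 34–64 or 64–100. This stands, and it is the main reason to treat the point as minor.

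2. **The error is on the safe side.** Under the stated effects, the printed group sizes give 80% power or more. Correcting them to 34–64 makes the claim of adequate power easier to support. This also stands, but only if the effect range is the correct half of the sentence.

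3. **Feasibility has a second support.** The 5 mmHg calculation is right, and it is set against the cohort size directly. This stands. The power sentence does not depend on the faulty line alone.

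4. **The wording is approximate.** This does not stand. A qualifier cannot cover the gap between 34 and 100, nor explain why the range runs upward from 64.

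A reader might go further and infer that the study is underpowered, or that it needs 74% attendance after 20 years. The document supports neither. The 74% belongs only to the 0.4 SD end of one possible correction; it is not required by 0.5–0.7 SD or by the worked example. A reader might also fault the section for giving no retention forecast, or for not listing detectable differences by attendance. A condensed article commonly leaves such detail to the full protocol. Figures in mmHg taken from this section would also rest on a systolic SD and an unadjusted comparison, whereas sections 2.5 and 2.5.2 name mean arterial pressure as the primary outcome and plan analysis of covariance.

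**Conclusion.** The point holds as an internal inconsistency of minor weight. The effect range and the sample-size range in section 2.5.1 cannot both be right: at 0.7 SD the requirement is about 34 per group, and 100 per group belongs to 0.4 SD. This rests on a two-sided 5% test, 80% power, equal groups and an unadjusted comparison of means, which are the conditions that reproduce the protocol's own 64 per group.

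Which range is wrong cannot be settled from the document, because the 0.5–0.7 SD figure is taken from a cited source that is not at hand. If the effect range is right, the mistake is conservative and the power conclusion is strengthened by correcting it. If the group sizes are right, the planned effects are 0.4–0.5 SD, and the conclusion is less secure at the lower effect. The blood pressure calculation is correct in either case.

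**What to change.** Check the cited source for the effect range, then correct one half of the sentence:

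- keep 0.5–0.7 SD and give the requirement as about 34–64 per group; or
- keep 64–100 per group and give the effect range as 0.4–0.5 SD.

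Then reword the power sentence to match the range kept. Under the second option it should acknowledge that the smaller effect would need 200 of the 269 pairs. The worked example needs no change. The cost is a text correction only, with no effect on procedures, data collection or analysis.

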#### Data analysis

2.5.2.

The differences between the intervention and control group in primary and secondary outcomes will be analyzed separately for the mothers and offspring. We will follow the CONSORT guidelines (47–49). The primary outcome, blood pressure, and the majority of the secondary outcomes are continuous with two time points: baseline and a 20-year follow-up. Analysis of covariance will be used to analyze the data (50). There may be some selection of participants in a long-term follow-up. We can adjust for variables that differ between the intervention and control group and are associated with the outcome of interest (48). However, the use of analysis of covariance (i.e., adjustment for the baseline value) may have to be evaluated if there are major indications of selective drop-out. In that case, we will analyze the difference between the values observed at the 20-year follow-up and the baseline using a multivariable linear regression model and adjust for potential covariates.

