### Design and setting

2.2.

The CARRDIP study was an RCT with dietary intervention in pregnancy performed between 1999 and 2001. The participating mothers were allocated to either the intervention group (*n* = 141) or the control (*n* = 149) group. The aim of the intervention group was to limit dietary cholesterol to 150 mg/day and reduce the intake of saturated fat to 8% of the total energy intake. The intended composition of the total energy intake consisted of 32% from total fat, 16%–17% from protein, and 50%–51% from carbohydrates. The intervention group was encouraged to increase the intake of fatty fish, olive oil, nuts, and avocado to replace meat, butter, and fatty dairy products and to replace full-fat dairy products with skimmed or low-fat ones. The control group consumed their usual diet and did not introduce oils or low-fat meat or dairy products, aiming at 32% of energy from total fat (including 12% from saturated fat), 16%–17% of energy from protein, and 50%–51% of energy from carbohydrates. Total energy intake aimed at a weight gain of 8–14 kg during pregnancy in both study groups (26). The participants were monitored several times during pregnancy with planned follow-up visits at gestation weeks 24, 30, and 36. Mothers and offspring were followed up, both to ensure adherence to the Mediterranean diet in the intervention group and to monitor the health status of both the mother and the fetus (fetal biometric measurements and Doppler measurements). Blood lipid levels, markers of endothelial activation, and inflammation were measured in maternal samples during pregnancy and in cord blood at birth. Several pregnancy and birth outcomes were recorded, and neonatal lipid levels were measured. The CARRDIP study found a significant reduction in the umbilical artery pulsatile index, reflecting decreased placental vascular resistance (27). This reduction in the index between gestational weeks 24 and 30 was a significant predictor of higher systolic blood pressure at 6 months of age, supporting the concept of fetal origins in the development of cardiovascular risk factors (30).

The current CARRDIP20 study will be a long-term follow-up of all mothers and their offspring separately, comparing the effects of intervention against control in both groups.

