### Outcomes

2.5.

The primary and secondary outcomes will be based on the findings and sampling methods of the original study and of similar studies on nutritional status during pregnancy (23, 26–28, 30, 33–39). The assessment, analysis, and reporting of outcomes will follow relevant CONSORT guidelines for clinical trials, and the current study protocol will adhere to the SPIRIT (Standard Protocol Items: Recommendations for Interventional Trials) guidelines (40, 41).

The primary outcome of the study will be the difference in the mean arterial blood pressure between the control and intervention groups in the CARRDIP offspring group due to hypertension being one of the most important CVD risk factors (42). Maternal exposures during pregnancy have been found to potentially influence offspring's blood pressure and contribute to the development of CVD risk factors later in life. Factors such as maternal smoking, alcohol consumption, or diet have been associated with an increased risk of elevated blood pressure levels in the offspring. In addition, these maternal exposures have been linked to developing other CVD risk factors in the offspring, including dyslipidemia, insulin resistance, obesity, and impaired glucose metabolism (33, 43, 44). Moreover, we have previously collected blood pressure measurements among the offspring at both 1-year and 3-year follow-up visits. Thus, the blood pressure variable presents an opportunity for further analysis on parameters tracking from birth, through childhood, and into early adulthood.

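### The primary analysis adjusts offspring blood pressure for a baseline that cannot exist before the intervention, and the change-score fallback relies on the same value

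*Protocol article*

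**What the plan says.** Section 2.5 (Outcomes) of the protocol article defines the primary outcome: "The primary outcome of the study will be the difference in the mean arterial blood pressure between the control and intervention groups in the CARRDIP". The sentence goes on to make clear that the children are meant, not the mothers.

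Section 2.5.2 (Data analysis) covers mothers and offspring in one paragraph, to be analysed separately but with the same model. It states: "The primary outcome, blood pressure, and the majority of the secondary outcomes are continuous with two time points: baseline and a 20-year follow-up". The method is analysis of covariance, and the paragraph says what it means by that: "the use of analysis of covariance (i.e., adjustment for the baseline value) may have to be evaluated if there are major indications of selective drop-out". If drop-out is selective, the plan switches to a regression on the 20-year value minus the baseline value, with covariates.

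On timing, section 2.3 (Participants) says: "Eligible participants were included after an ultrasound showing a single healthy fetus in gestational weeks 17–20". The abstract places the diet in pregnancy.

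The earlier offspring pressures named are at 6 months (section 2.2) and at 1 and 3 years. On the latter, section 2.5 says: "we have previously collected blood pressure measurements among the offspring at both 1-year and 3-year follow-up visits".

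**The concern.** For the mothers, a value taken at inclusion is a proper baseline. For the offspring there is none. At inclusion the child was a fetus, and by the time its blood pressure could be measured the diet had ended. Yet section 2.5.2 asserts a baseline for exactly this outcome and makes both of its models depend on it.

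An analyst following the text must either leave the covariate out, which departs from the plan, or pick one of the childhood pressures. The second route conditions on something measured after randomisation. If the diet changed early blood pressure, the group coefficient is no longer the total effect of the diet, which is what the study sets out to compare. The article itself gives a reason to keep that possibility open. Section 2.2 reports that the original trial found a reduced umbilical artery pulsatile index, and that the reduction between weeks 24 and 30 "was a significant predictor of higher systolic blood pressure at 6 months of age".

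Because the article does not say which early value, if any, would serve, that choice could also be made after the 20-year data are seen.

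**Working it through.** **1. Is there a baseline?** Set side by side, the sections do not fit together:

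- Outcome: blood pressure of the offspring (section 2.5).
- Time points asserted: baseline and 20 years (section 2.5.2).
- State of the offspring at inclusion: fetus, weeks 17–20 (section 2.3).
- Intervention period: pregnancy (abstract).
- Earlier offspring pressures: 6 months, 1 year, 3 years (sections 2.2 and 2.5), all after the intervention.

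No pre-intervention value is possible, and no substitute is defined. The fallback subtracts the same missing value.

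**2. The plan's own figure.** Section 2.5.1 assumes a systolic difference of 5 mmHg, SD 10, 80% power and 5% significance (two-sided assumed), and gives 64 per group. The normal formula gives n = 2 × (1.960 + 0.842)² × 10² / 5² = 62.8, so 63 per group. The t-test gives 63.77, so 64 per group with 80.1% power. The figure reproduces. It is an unadjusted two-group comparison that takes no credit for a baseline covariate.

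**3. What an early value would do as covariate.** The article gives neither of the two quantities needed, so both are assumed:

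- g, the effect of the intervention on early pressure: 0.2 to 0.5 SD, in either direction.
- r, the within-arm slope of adult on early pressure: 0.2 to 0.5. It equals the correlation when the SD is 10 at both ages, which is also assumed.

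With a true total difference of 5 mmHg:

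- Covariance analysis estimates 5 − 10·r·g.
- Change score estimates 5 − 10·g.

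| Early effect relative to adult effect | Covariance analysis | Change score |
|---|---|---|
| Same sign, g = 0.2, r = 0.2 | 5 − 0.4 = 4.6 | 5 − 2 = 3.0 |
| Same sign, g = 0.5, r = 0.5 | 5 − 2.5 = 2.5 | 5 − 5 = 0 |
| Opposite sign, g = 0.2, r = 0.2 | 5 + 0.4 = 5.4 | 5 + 2 = 7.0 |
| Opposite sign, g = 0.5, r = 0.5 | 5 + 2.5 = 7.5 | 5 + 5 = 10.0 |
| No early effect (g = 0) | 5.0 | 5.0 |

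**4. Precision of the fallback when g = 0.** The change score has SD 10 × √(2(1 − r)). With 64 per group, power = Φ(5 / (SD × √(2/64)) − 1.96):

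| r | SD of change | Power at 64 per group | Needed per group for 80% |
|---|---|---|---|
| 0.1 | 13.42 | 56% | 114 |
| 0.2 | 12.65 | 61% | 101 |
| 0.3 | 11.83 | 67% | 88 |
| 0.5 | 10.00 | 81% | 63 |

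So even without bias, the fallback falls short of the planned power when early and adult pressure correlate weakly.

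**The case against.** The strongest reply is that nothing shows any harm. No section reports a between-arm difference in blood pressure at 6 months, 1 year or 3 years; section 2.2 reports an association with a predictor. If the diet left early pressure unchanged, adjusting for it is unbiased and gains precision: at 64 per group, power would be about 81% at r = 0.1 and 90% at r = 0.5. The paragraph may also be a maternal analysis carried over to the children, and section 2.5 offers the childhood pressures for tracking, not as the covariate. All of this stands. It limits what can be said about bias, but it does not supply the baseline that the paragraph asserts.

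A reader might infer four stronger points that the article does not support:

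- *The analysis cannot be run.* Early pressures exist, so a model could be fitted. The fault is that none of them is a pre-randomisation baseline and none is named as the covariate.
- *The effect will be diluted.* The one link reported runs from a lower pulsatility index to higher pressure at 6 months. If the adult effect is a reduction, the bias could inflate it instead.
- *Adjusting for neonatal cholesterol would remove the pathway that the trial set out to change.* Section 2.5.1 says the original trial "was designed to detect a clinically relevant difference in maternal cholesterol levels at week 36 in pregnancy and in neonatal cholesterol levels". That makes neonatal cholesterol a target, not a documented effect, and the article never names it as a covariate.
- *Carotid, liver and body-composition measures share the error.* Section 2.5.2 claims a baseline only for most secondary outcomes and does not say that these are among them.

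**Conclusion.** Wrong as written. The plan states a baseline time point for its primary outcome that cannot precede the intervention, and both specified models depend on it. This is a positive statement that conflicts with sections 2.3 and 2.5, not a detail left to a fuller document. It follows from the text without any assumption.

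The consequence is conditional. If a childhood pressure is used as the baseline, the estimate may not be the total effect of the diet, and neither the size nor the direction of the bias can be derived from the article. The ranges (2.5 to 7.5 mmHg for the covariance analysis and 0 to 10 mmHg for the change score, against a true 5) rest wholly on the assumed early effect, slope and equal SDs. The fault is specific to the offspring; for maternal outcomes measured before the intervention, the method may be sound.

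**What to change.** Reword section 2.5.2 as follows.

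- Restrict baseline-adjusted analysis of covariance, and the change-score fallback, to maternal outcomes measured before the intervention.
- For offspring outcomes, fit a linear model of the 20-year value on randomised group, adjusted only for variables fixed before randomisation: for example offspring sex, maternal age and BMI at inclusion, and maternal blood pressure at inclusion if it was recorded.
- State that cord-blood, neonatal, 6-month, 1-year and 3-year values are post-randomisation data. They may inform imputation, repeated-measures or tracking analyses, but are not covariates in the effect estimate.
- For selective drop-out among the offspring, replace the change score with a method that needs no offspring baseline, such as multiple imputation or weighting that uses the earlier data.

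The cost is one paragraph and no new data. The sample size stays at 64 per group, since it already rests on an unadjusted comparison. The change should be fixed before the 20-year data are compared by group.

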The Cardiovascular Risk Reduction Diet in Pregnancy (CARRDIP) study was an RCT that examined the effects of a Mediterranean diet intervention on both maternal and fetal outcomes among healthy pregnant women (26–30). Some important study findings were identified in this study, including differences in the fatty acid composition in the blood and a reduction of low-density lipoprotein levels in the serum during pregnancy. In addition, the intervention group exhibited a decrease in the instances of premature births compared with the control group. While the CARRDIP study focused on the immediate health effects, we now want to examine the long-term health effects on both mothers and offspring in the CARRDIP cohort. In this study, we describe the protocol for CARRDIP20, a follow-up study conducted 20 years after the original randomized controlled trial involving dietary intervention in pregnancy.

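### The covariate rule is data-driven and not limited to pre-randomisation variables, so it admits variables the diet itself changed and can bias the randomised effect in either direction

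*Protocol article*

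**What the plan says.** Section 2.5.2 plans analysis of covariance on the baseline value for blood pressure and most secondary outcomes. It then raises attrition: "There may be some selection of participants in a long-term follow-up". The remedy offered is: "We can adjust for variables that differ between the intervention and control group and are associated with the outcome of interest". No variable is named and no time limit is set. If drop-out appears strongly selective, the plan moves to change from baseline, "using a multivariable linear regression model and adjust for potential covariates", again without saying which covariates.

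Elsewhere the article reports what the diet changed during pregnancy. Section 2.2 (Design and setting) states: "The CARRDIP study found a significant reduction in the umbilical artery pulsatile index, reflecting decreased placental vascular resistance". It adds that this reduction, between gestational weeks 24 and 30, "was a significant predictor of higher systolic blood pressure at 6 months of age". The Introduction reports lower maternal low-density lipoprotein (LDL) in the intervention group and that "the intervention group exhibited a decrease in the instances of premature births compared with the control group". It also notes that maternal and offspring cholesterol are correlated from 6 months to 6 years.

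The primary outcome (section 2.5) is "the difference in the mean arterial blood pressure between the control and intervention groups in the CARRDIP offspring group". Offspring lipid profile is a secondary outcome.

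**The concern.** In a randomised comparison, a variable measured after allocation that differs by arm and predicts the outcome is a natural candidate for a mediator. The two conditions in the rule are the ones a mediator meets. The rule cannot tell a pre-randomisation variable unbalanced by attrition, which is its apparent target, from a variable the diet altered.

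The design makes this more than a formality. Women entered after an ultrasound in gestational weeks 17–20 (section 2.3), so almost everything measured on the offspring comes after randomisation.

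Two things are at stake. The estimate may no longer be the total effect of randomised diet, which is what the primary outcome describes. And because covariates are picked after seeing which variables differ by arm, the primary model becomes a choice made on the data. That is a drawback even among true baseline variables, because a strong predictor that happens to be balanced would be left out.

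**Working it through.** **1. Which documented variables meet both conditions?**

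- *Umbilical artery pulsatile index:* arm difference stated and association with offspring systolic pressure stated (section 2.2). Both are met, although the association is at 6 months, not 20 years. The diet lowers the index and the reduction predicts higher pressure, so this path runs towards higher pressure in the intervention arm.
- *Maternal LDL in pregnancy, for the offspring lipid outcomes:* arm difference stated, and maternal cholesterol correlates with offspring cholesterol (Introduction). Both are met up to age 6 years. Lower maternal LDL points towards lower offspring cholesterol, so adjustment would pull a lipid benefit towards zero.
- *Preterm birth:* arm difference stated, but no link to later blood pressure. Only the first condition is shown.
- *Current BMI, waist and diet:* collected at 20 years. The article documents no arm difference.

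**2. The plan's own figure.** Section 2.5.1 assumes 5 mmHg, SD 10, 80% power and 5% significance (taken as two-sided). The normal approximation is n = 2 × (1.96 + 0.84)² × 10² / 5² ≈ 63 per group. The t-test gives 63.8, so 64 per group and 128 in all, as stated. The figure is for systolic pressure; it serves here only to set the scale.

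**3. What the rule does to the estimate.** These inputs are assumptions, since the document gives none of them:

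- One post-randomisation variable M, with SD 1 within arm, shifted 0.5 SD by the diet.
- Total effect = direct effect + effect through M, with slope of outcome on M = (effect through M) / 0.5. Paths of 1.25, 2.5 and 3.75 mmHg therefore need slopes of 2.5, 5 and 7.5 mmHg per SD. With an outcome SD of 10, these are within-arm correlations of 0.25, 0.50 and 0.75; the last is extreme.
- M enters the model if it differs by arm (p < 0.05) and is associated with the outcome given arm (p < 0.05). The article sets no thresholds.
- 64 per arm, 6,000 simulated trials per row.

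| True total effect (mmHg) | Part through M | M selected | Mean estimate, unadjusted | Mean estimate, rule applied | Rejections, unadjusted | Rejections, rule applied |
|---|---|---|---|---|---|---|
| −5 | 0 | 4% | −5.01 | −5.01 | 80% | 80% |
| −5 | −1.25 | 66% | −5.00 | −3.98 | 80% | 60% |
| −5 | −2.50 | 81% | −5.02 | −2.75 | 80% | 39% |
| −5 | −3.75 | 79% | −4.97 | −1.64 | 80% | 22% |
| −5 | +1.25 | 65% | −4.97 | −5.99 | 80% | 91% |
| −5 | +2.50 | 79% | −4.96 | −7.19 | 80% | 99% |
| 0 | +2.50 | 80% | −0.06 | −2.30 | 4% | 30% |

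The first row is the control case: a variable the diet shifts but which does not affect the outcome does no harm. Rows 2–4 show attenuation when the path runs with the effect. Rows 5–6 show exaggeration when it runs against it, the direction reported for the pulsatile index. In the last row there is no total effect, and the rule rejects in 30% of trials against 4% unadjusted (nominal 5%).

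**The case against.** The strongest reply is that the sentence is permissive and sits directly after the remark on selection at follow-up. Read in context, it is an optional remedy for imbalance caused by attrition. Pre-randomisation variables unbalanced by drop-out fit it as well as any mediator. It names no mediator, the main analysis remains analysis of covariance on baseline, and an exact covariate list may stand in a full protocol or analysis plan that is not shown.

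Much of this stands. The absence of a covariate list is not the point here. What the article does state is a criterion for choosing covariates, and that criterion is unsound as written. Making it optional does not help, because it leaves the choice of primary model open until the arm differences are known.

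A reader might also infer that the rule selects preterm birth and placental resistance and so adjusts the diet effect away. The document does not support that. The rule allows such variables but does not prescribe them. For preterm birth no association with later blood pressure is given. For placental resistance the reported association runs the other way, so adjustment could enlarge or create an apparent lowering of blood pressure. A calculation of lost power alone would show only one side. For example, a shift of 0.3–0.5 SD with outcome correlations of 0.2–0.4 removes 0.06–0.20 SD and takes power from 80% to about 69%–39%. The arithmetic is right, but both inputs and the sign are assumed.

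**Conclusion.** The concern holds in this form: the stated rule is data-driven, is not limited to pre-randomisation variables, and can therefore admit variables the diet changed and bias the total effect in either direction. The pulsatile index (for blood pressure) and maternal LDL (for offspring lipids) show that the risk is not hypothetical, though neither association is documented at 20 years.

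The size cannot be fixed from the document. In the illustration a true −5 mmHg is reported on average as anything from −1.64 to −7.19 mmHg, depending on the sign and strength of an assumed path through one variable shifted 0.5 SD, with the rule always applied. A general bias towards zero, or a definite loss of power, is not established. The sample size calculation is unaffected.

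**What to change.** Replace the sentence in section 2.5.2 with a covariate set fixed before arm-level data are examined. Suitable wording: *Between-arm models include a fixed set of maternal variables recorded before randomisation (for example age and BMI at inclusion) and offspring sex, whether or not they are balanced. Offspring age at examination is also included, as the one exception to the limit on later measurements. No other variable measured after randomisation enters a between-arm model.*

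- Apply the same limit to the unspecified covariates of the fallback change-from-baseline model. State in the same place what baseline means for offspring blood pressure: the offspring were fetuses at inclusion, so any infant or childhood pressure falls under the limit.
- Handle selective follow-up separately, as a sensitivity analysis, for example by inverse-probability weighting or multiple imputation using data from the original trial. Post-randomisation variables may inform the model for who attends, or the imputation model, without entering the between-arm model as covariates.
- Use Doppler indices, preterm birth, maternal lipids in pregnancy, birth weight and current BMI or diet only in a separately labelled exploratory mediation analysis.

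The cost is about one paragraph, slightly more analysis work, and less freedom to choose covariates after seeing the data. Age and BMI were entry criteria in the original trial, so they should be on file. Other candidates, such as parity or maternal blood pressure at inclusion, should be listed only after confirming that they were recorded, since the article does not say so.
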